### 2.10 Sample size calculation

In a previous study (Xu, 2017), JTTF reduced HbA1c levels in diabetic patients with heat stagnation in liver and stomach after 12 weeks of treatment (treatment group: 6.94±0.88%, control group: 7.64±0.72%, mean difference between the two groups: 0.7%). Considering a type I error of 5% (α = 0.05) and a power of 85%, the experimental and control groups were allocated at a ratio of 1:1. The sample size was calculated using Power Analysis and Sample Size (PASS) software (version 15.0); a total of 76 patients will be required. According to the dropout rate of 20%, we set the final sample size to 96, with 48 patients in each group, considering the number of dropout samples.

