## Abstract

**Background:** The incidence of Type 2 diabetes mellitus (T2DM) combined with non-alcoholic fatty liver disease (NAFLD) has risen over the years. This comorbid condition significantly increases the probability of cirrhosis, liver cancer, and mortality compared to the disease alone. The multi-targeted, holistic treatment efficacy of traditional Chinese medicine (TCM) plays a vital role in the treatment of T2DM and NAFLD. Jiedu Tongluo Tiaogan Formula (JTTF), based on TCM theory, is widely used in clinical treatment, and its effectiveness in lowering glucose, regulating lipids, improving insulin resistance, and its pathways of action have been demonstrated in previous studies. However, the mechanism of this formula has not been investigated from a metabolomics perspective. Moreover, high-quality clinical studies on T2DM combined with NAFLD are lacking. Therefore, we aim to conduct a clinical trial to investigate the clinical efficacy, safety, and possible pathways of JTTF in the treatment of T2DM combined with NAFLD using metabolomics techniques.

**Methods:** A total of 98 participants will be recruited to this clinical trial and randomly assigned to either a treatment group (JTTF + conventional basic treatment) or control group (conventional basic treatment) in a 1:1 ratio. Both groups will have received the same lifestyle interventions in the preceding 12 weeks. The primary outcome will be change in visceral fat area and total score on the TCM syndromes efficacy score scale. The secondary outcome will include changes in ultrasound steatosis grade, fibrosis 4 score (FIB-4), metabolic parameters, anthropometric parameters, visceral fat area. In addition, serum and urine samples collected at baseline and at the end of 12 weeks of treatment will be sequentially tested for untargeted and targeted metabolomics.

**Discussion:** This study will evaluate the efficacy and safety of JTTF, as well as investigate the differential metabolites and possible mechanisms of JTTF treatment in T2DM combined with NAFLD. We hypothesize that patients will benefit from JTTF, which may provide strong evidence for the clinical use of JTTF in the treatment of T2DM and NAFLD, leading to the possibility of further mechanistic exploration.

**Clinical Trial Registration:** This clinical trial has been registered in China Clinical Trial Registry (ChiCTR 2100051174).

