#### 2.8.2 Primary outcomes

The primary outcome is change in visceral fat area (VFA) and TCM syndromes efficacy score scale. Changes in VFA will be compared between the two groups before and after treatment. The indicator will be tested at baseline and week 12. The TCM symptom scoring standard is presented in Supplementary Material S3.

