#### 2.8.3 Secondary outcomes

1) Changes in hepatic steatosis factors by ultrasound grading of steatosis.2) Changes in metabolic parameters: glycated hemoglobin (HbA1c) levels, fasting plasma glucose (FPG), 2-h plasma glucose (2h-PG), fasting insulin, blood lipids including total cholesterol (TC), triglycerides (TG), high-density lipoprotein-cholesterol (c-HDL), low-density lipoprotein (c-LDL), apolipoprotein A (ApoA), and apolipoprotein B (ApoB).3) Changes in anthropometric parameters: Waist-to-height ratio (WHtR), Body Mass Index (BMI), waist circumference (WC), hip circumference (HC).4) Changes in hepatic fibrosis factors and hepatic function: The changes in Fibrosis 4 Score (FIB-4, http://gihep.com/calculators/hepatology/fibrosis-4-score/) can be calculated by the formula:

$$\mathrm{Age}\;\left(\mathrm{years}\right)\text{x}\;\mathrm{AST}\;/\mathrm{PLT}\;\left(\times 10^{9}/L\right)\text{x}\sqrt{\mathrm{ALT}}$$

The units of measurement for ALT and AST are aligned with those for age and PLT.

Definitions for the following abbreviations: AST: Aspartate aminotransferase; PLT: platelet; ALT: Alanine aminotransferase.5) Changes in visceral fat area.

All measurements will be performed at baseline and at week 12. Additional FPG and blood lipid test will be performed at week 6.

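### The sample size and its 85% power rest on HbA1c, a secondary outcome; no power is given for VFA or the TCM score, and 85% does not follow from the HbA1c inputs either

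*Protocol article*

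**What the plan says.** Section 2.8.2 defines the primary endpoint: "The primary outcome is change in visceral fat area (VFA) and TCM syndromes efficacy score scale". The Abstract agrees: "The primary outcome will be change in visceral fat area and total score on the TCM syndromes efficacy score scale". Section 2.8.3 places HbA1c among the secondary outcomes, under item 2: "Changes in metabolic parameters: glycated hemoglobin (HbA1c) levels".

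Section 2.10 takes its effect from a previous study in which "JTTF reduced HbA1c levels in diabetic patients with heat stagnation in liver and stomach after 12 weeks of treatment". The figures carried over are "treatment group: 6.94±0.88%, control group: 7.64±0.72%, mean difference between the two groups: 0.7" (percentage points of HbA1c). The calculation uses alpha 0.05 with sidedness not stated, 85% power and equal allocation. It arrives at 76 participants, raised to 96 (48 per arm) for 20% dropout. The section contains no expected difference or SD for VFA or the TCM score, and nothing that links the HbA1c effect to either of them.

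**The concern.** A sample size section exists to show that the primary analysis can detect an effect worth detecting. Here the endpoint in the calculation and the endpoints of the primary analysis are different variables on different scales. Power for one says nothing about power for the other unless their standardised effects are known to be similar, and the article does not say that they are.

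The stake is interpretation. If VFA shows no significant difference, a reader who sees 85% beside the sample size may take the result as good evidence against an effect. Whether it is depends on a standardised VFA effect that the article never gives. The same holds for the TCM score.

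**Working it through.** **Inputs.** From section 2.10: HbA1c difference 0.7; SDs 0.88 and 0.72; alpha 0.05; power 85%; 1:1 allocation; 76 evaluable (38 per arm); 20% dropout. Two-sided testing is my assumption. The independent-samples t-test is the one named in section 3.1 for normally distributed data.

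**Step 1: reproduce the plan's 76.**
- Common SD = √((0.88² + 0.72²)/2) = √((0.7744 + 0.5184)/2) = 0.804.
- Standardised difference d = 0.7/0.804 = 0.871.
- Normal approximation: n per arm = 2(1.960 + 1.036)²/0.871² ≈ 23.7, so 24 per arm, 48 in total.
- Exact (noncentral t): 25 per arm, 50 in total.
- One-sided alpha 0.05: 38 in total (normal) or 40 (exact).
- The larger SD, 0.88, throughout, two-sided: 58 (normal) or 60 (exact).

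None of these is 76. The exact two-sided t calculation does return 76 if 0.7 is entered as the standardised difference, that is, with SD = 1. That this happened is only an inference.

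**Step 2: HbA1c power at the planned size.** With 38 per arm the noncentrality is d√(n/2) = 0.871 × √19 ≈ 3.80 on 74 degrees of freedom. Power is 96.3% (96.7% by the normal approximation), not 85%.

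**Step 3: dropout.** 76/(1 − 0.20) = 95, rounded up to 96 for equal arms. This step is sound.

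**Step 4: what 38 per arm gives for a primary outcome.** The documents supply no effect for VFA or the TCM score, so the effects below are assumptions on the SD scale. They lie on both sides of the detectable difference.

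| Assumed effect (SD) | Power, 38 per arm, two-sided 0.05 | Total evaluable for 85% power |
|---|---|---|
| 0.3 | 25% | 402 |
| 0.4 | 41% | 228 |
| 0.5 | 58% | 146 |
| 0.6 | 73% | 102 |
| 0.7 | 85% | 76 |
| 0.8 | 93% | 60 |

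The smallest effect with 85% power is 0.697 SD at alpha 0.05. It is 0.765 SD at alpha 0.025, which applies only if alpha is split between the two primaries. If all 48 per arm were evaluable, it would be 0.618 SD at alpha 0.05.

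**The case against.** Section 2.10 names HbA1c openly and never attributes the 85% to VFA or the TCM score. HbA1c is not an arbitrary choice either: the hypothesis under the primary objective (section 2.1.1) includes lowering blood glucose, and the Discussion names glucose lowering among the trial's aims. Both points are fair. They make the choice understandable, but they do not make HbA1c a primary outcome or give either primary a power.

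A reader might infer more than the documents support, in three ways.

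- **That the trial is underpowered for its primaries.** This cannot be shown. If the true VFA or TCM-score effect is 0.7 SD or more, 76 evaluable participants are enough, and the article gives no basis for expecting a smaller effect rather than a larger one. The power is undocumented, which is different from low.
- **That 85% is at least correct for HbA1c.** Step 2 contradicts this. A note saying that 85% applies to HbA1c only would replace one wrong statement with another.
- **That alpha should have been 0.025.** A split is needed if success on either primary suffices. If both must succeed, each can be tested at 0.05, and joint power falls instead. Section 2.8.2 does not settle which applies. Multiplicity and the interim look in section 3.2 are separate matters, and this point does not rest on them.

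It could also be said that a change of wording alters no design or analysis, and that recruitment was already under way (section 5). That is true, and it limits what is asked for. The stated power still bears directly on how the primary result will be read.

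**Conclusion.** The point holds. The only power figure in the article belongs to a secondary outcome, and it is not the power that the stated HbA1c inputs give: about 96% at 38 per arm, against 85% stated; about 50 evaluable needed, against 76 stated. For VFA and the TCM score the plan supports one statement: 85% power for a standardised difference of about 0.70 or more, with 38 evaluable per arm and two-sided alpha 0.05.

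The mismatch of endpoints rests on the text alone and needs no assumption. The HbA1c figures assume a two-sample t-test, two-sided; the one-sided variants do not reach 76 either. The power range for the primaries rests on assumed effects and shows what is unknown, not that the trial is too small.

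**What to change.** Keep N at 96, the figure in sections 2.2 and 2.10, and restate section 2.10 as follows.

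1. Make the HbA1c calculation and its inputs agree. Either correct the number that follows from 0.7, 0.88 and 0.72, or state the SD that was actually used and its source. Label the calculation as referring to a secondary outcome.
2. For VFA and for the TCM score separately, state that 76 evaluable participants give 85% power only for a standardised difference of about 0.70, or about 0.77 if the protocol chooses to split alpha between the two. Convert each to natural units (cm² and score points) with a sourced SD; the article contains none.
3. Do not present 85% as the power of the primary analysis. State whether alpha is one- or two-sided.

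The cost is rewording and a search for two SDs. No participant, visit or analysis changes. The drawback is that the stated power for the primaries becomes less favourable: the 85% is replaced by a detectable difference that the sponsor may find large once it is in natural units.

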### 2.2 Study design

This study is designed as a 12-weeks, single-center, double-armed, parallel, randomized, controlled clinical trial. A total of 96 eligible participants will be recruited from Shenzhen Hospital of Guangzhou University of Chinese Medicine (Futian) and randomized in a 1:1 ratio into two groups to receive basic treatment. As a supplement to the clinical study, participants’ fasting serum and urine samples will be subjected to untargeted and targeted metabolomic assays. Liquid chromatography–mass spectrometry (LC-MS) will be used to compare metabolites before and after treatment in the experimental and control groups. Basic analysis of metabolites, multivariate statistical analysis, pathway enrichment analysis, and topological analysis of the screened differential metabolites will be performed.

All patients should have voluntarily participated and signed an informed consent form with good compliance. Informed consent will be obtained from all participants prior to enrollment. A flowchart and schedule of the clinical trial is shown in Figure 1 and Table 1, respectively. The protocol was designed according to the Standard Protocol Items: Recommendations for Interventional Trials (SPIRIT) guidelines (Chan et al., 2013) and the Declaration of Helsinki. The SPIRIT checklist is shown in Supplementary Material S2.

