## 3 Statistical methods

### 3.1 Data analysis

Data will be analyzed using SPSS software (Version 24.0; IBM Corp. Armonk, NY, United States). Continuous variables will be represented as means, standard deviations, medians, and minimum/maximum values. If the data confirms normal distribution, an independent sample *t*-test will be used to assess the differences between the two groups, and a paired sample *t*-test to compare the differences between groups before and after the intervention. Wilcoxon signed-rank test will be used for data that does not conform to normal distribution. Grade data will be analyzed using Wilcoxon’s signed-rank test or the CMHχ2 test. Statistical significance will be set at *p* < 0.05.

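### The 76 patients cannot be reproduced from the HbA1c inputs printed beside them (about 50 if two-sided), and the abstract's total of 98 disagrees with the body's 96

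*Protocol article*

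**What the plan says.** Section 2.10 (Sample size calculation) takes 12-week HbA1c from a previous study of the formula: "treatment group: 6.94±0.88%, control group: 7.64±0.72%, mean difference between the two groups: 0.7", all in percentage points. It sets the error rates with the words "Considering a type I error of 5% (α = 0.05) and a power of 85" (per cent), uses 1:1 allocation, names PASS 15.0 as the software, and concludes that "a total of 76 patients will be required". It then allows for 20% dropout and arrives at 96, or 48 per group.

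Section 3.1 (Data analysis) names an independent-sample t-test for the between-group comparison of normally distributed data, and gives the threshold as "Statistical significance will be set at *p* < 0.05". Neither section says whether tests are one-sided or two-sided.

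The total appears in two forms. The abstract says "A total of 98 participants will be recruited to this clinical trial". Section 2.2 (Study design) says "A total of 96 eligible participants will be recruited", which agrees with section 2.10.

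HbA1c is listed under secondary outcomes (section 2.8.3). The primary outcomes are visceral fat area and the TCM syndrome score (section 2.8.2).

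**The concern.** Section 2.10 prints everything that a two-mean calculation needs, so a reader can check it. The quoted difference is nearly 0.9 of a standard deviation, and 38 per arm is well above what a t-test needs for an effect that large at 85% power. Either an input that mattered was not printed, or the result or the power is misstated.

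This calculation is the only justification given for the size of the trial. As printed, it cannot be verified, and the 85% does not describe what 76 patients deliver for the quoted effect. The two totals add a smaller inconsistency: the recruitment target differs by two, and the interim analysis at 50% enrolment (section 3.2) would fall at 49 by the abstract and 48 by the body.

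**Working it through.** **Inputs.** From section 2.10: means 6.94 and 7.64, so the difference is 0.70; SDs 0.88 and 0.72; alpha 0.05; power 0.85; allocation 1:1; stated result 76 (38 per arm); dropout 20%. From section 3.1: independent-sample t-test. Assumed: two-sided, with one-sided also tried.

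**Step 1: standardised effect.**
SD = √[(0.88² + 0.72²)/2] = √[(0.7744 + 0.5184)/2] = √0.6464 = 0.804.
d = 0.70/0.804 = 0.871.

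**Step 2: attempt to reproduce 76, two-sided.**
Normal approximation: n per arm = 2(1.960 + 1.036)² / 0.871² = 23.7, so 24 per arm, 48 in total.
t-test (noncentral t): power is 0.840 at 24 per arm and 0.855 at 25 per arm, so 25 per arm, **50 in total**. Allowing unequal variances (Welch) gives power 0.854 at 25 per arm, the same answer.

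**Step 3: other readings of the printed inputs** (85% power, 1:1).

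| Reading | Total N |
|---|---|
| t-test, two-sided 0.05 | 50 |
| t-test, one-sided 0.05 | 40 |
| SD 0.88 in both arms, two-sided t-test | 60 |
| SD 0.72 in both arms, two-sided t-test | 42 |
| Two-sided alpha 0.025 (halved for two primary outcomes), t-test | 60 |
| Rank-test inflation of the two-sided 50 | 54 to 58 |
| Stated | 76 |

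None comes near 76. The gap from 50 is 26 patients, too large for rounding.

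**Step 4: power that 76 evaluable patients give.**
Noncentrality at 38 per arm = 0.70 / (0.804 × √(2/38)) = 3.795; the two-sided critical value on 74 df is 1.993. Power = **0.963**.
With SD 0.88 in both arms, power at 38 per arm is 0.928.
At 48 per arm with no dropout, using the 0.804 SD, power is 0.988.

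**Step 5: what would give 76 at 85% power.** Several unprinted inputs would:
- a common SD of about 1.0 with the 0.70 difference;
- a detectable difference of about 0.56 with the quoted SDs, equivalent to a superiority margin of about 0.14 at two-sided 0.05 (one-sided 0.025);
- a superiority margin of 0.2 at one-sided 0.05;
- doubling the one-sided normal-approximation total of 38 (2 × 19), as in a mix-up of total and per-arm size.

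None of these is stated.

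**Step 6: dropout and totals.** 76/0.8 = 95. Per arm, 38/0.8 = 47.5, rounded up to 48, so 96. This step is correct given 76. No stated step leads to 98. Starting from 50 instead, 50/0.8 = 62.5, so 63, or 64 for equal arms.

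**The case against.** **An unprinted input may explain 76.** A journal article condenses the full protocol, so a margin or a different SD may have been entered in PASS and left out. That stands, and it limits the claim to this: 76 is not reproducible from what is printed. It does not make the printed account right, because the article shows a full set of inputs with a result that they do not produce.

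**Two-sided testing is assumed.** Correct: neither section 2.10 nor section 3.1 states it. The one-sided requirement is 40, further from 76, so the mismatch does not depend on the assumption.

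**The discrepancy is conservative.** Correct for HbA1c: 76 exceeds the number that the inputs need. The harm is a misstated justification, not a loss of power for that effect.

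**Stronger readings that the document does not support:**
- *The 0.7 was entered as a standardised effect with SD 1.0.* That would give exactly 38 per arm, but so would the margins in step 5. A numerical match that is not unique does not show the cause.
- *The trial is too large and could be cut to about 64.* The calculation concerns a secondary outcome. A corrected HbA1c figure says nothing about the numbers needed for visceral fat area or the TCM score.
- *The recruitment target and interim trigger are undefined.* The body gives 96 twice and derives it, so 50% enrolment is 48. The 98 appears once, in the abstract, without derivation, and would move the trigger by one patient.

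**Conclusion.** The point holds as an error of statement. The printed inputs require about 50 evaluable patients (two-sided t-test, sidedness assumed) or 40 (one-sided), against the 76 stated. For the quoted HbA1c effect, 76 evaluable patients give about 96% two-sided power, or about 93% under the larger SD in both arms, against the 85% stated. The cause cannot be determined from the document. The dropout step from 76 to 96 is sound, and the abstract's 98 is inconsistent with it and with section 2.2. Correcting the figure leaves power for the two primary outcomes unaddressed. The point should be corrected, but it does not call for a change in enrolment.

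**What to change.** Keep 96 as the enrolment target and correct the text:

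1. In section 2.10, consult the PASS record. If an input that is not printed produced 76 (for example a margin, a different SD or a stated sidedness), print it. Otherwise keep the quoted means and SDs and state that 76 evaluable patients give about 96% power for the HbA1c difference at two-sided 0.05. An assumed SD of 1.0 should be written in only if the record shows it was used: it conflicts with the quoted SDs and would otherwise fit a rationale to a number.
2. State in section 2.10 whether alpha is one-sided or two-sided.
3. Change 98 to 96 in the abstract.

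The cost is a look at the software record and a few sentences of text. Enrolment, visits and analyses are unchanged.

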### 2.11 Recruitment

Participants in this clinical trial will be recruited mainly from outpatients and inpatients of the Endocrinology Department of the Guangzhou University of Chinese Medicine Shenzhen Hospital (Futian). Patients will also be recruited through posters and publicity on social media platforms. All examinations during the trial will be free of charge to participants. Members of the project team will conduct a detailed protocol explanation and screening of patients who volunteer to participate in the trial to ensure that participants fully understand the trial process and the inclusion criteria.

## 3 Statistical methods

### 3.1 Data analysis

Data will be analyzed using SPSS software (Version 24.0; IBM Corp. Armonk, NY, United States). Continuous variables will be represented as means, standard deviations, medians, and minimum/maximum values. If the data confirms normal distribution, an independent sample *t*-test will be used to assess the differences between the two groups, and a paired sample *t*-test to compare the differences between groups before and after the intervention. Wilcoxon signed-rank test will be used for data that does not conform to normal distribution. Grade data will be analyzed using Wilcoxon’s signed-rank test or the CMHχ2 test. Statistical significance will be set at *p* < 0.05.

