**FIGURE 1 F1:**
[figure not shown]
Flow chart of the clinical trial.

**TABLE 1 T1:** Schedule of the clinical trial.

Project time	Screening/baseline		Treatment			
	-14–0 days	0±2 days	Visit 1 4weeks± 2days	Visit 2 6weeks± 4days	Visit 3 8weeks± 6days	Visit 4 12weeks± 7days
Eligibility screening						
Inclusion/exclusion criteria	**✓**					
Informed consent form	**✓**					
Allocation	**✓**					
General information	**✓**					
Family history	**✓**					
Medical history	**✓**					
Drinking history	**✓**					
Physical examination^a^	**✓**	**✓**	**✓**	**✓**	**✓**	**✓**
Vital signs^b^	**✓**	**✓**	**✓**	**✓**	**✓**	**✓**
Ultrasound of liver	**✓**					**✓**
bioelectrical impedance analysis						
visceral fat area		**✓**				**✓**
subcutaneous fat area		**✓**				**✓**
Electrocardiography	**✓**			**✓**		**✓**
Laboratory examination						
Routine blood test		**✓**		**✓**		**✓**
Routine urine test		**✓**		**✓**		**✓**
Fasting blood sugar		**✓**		**✓**		**✓**
2-h plasma glucose		**✓**				**✓**
Glycated hemoglobin		**✓**				**✓**
Fasting insulin		**✓**				**✓**
Blood lipids		**✓**		**✓**		**✓**
Liver function		**✓**		**✓**		**✓**
Renal function		**✓**		**✓**		**✓**
Traditional Chinese medicine symptoms		**✓**	**✓**	**✓**	**✓**	**✓**
Fibrosis 4 Score		**✓**				**✓**
Homeostasis model assessment-insulin resistance		**✓**				**✓**
homeostatic model assessment for β-cell		**✓**				**✓**
Metabolomics test^c^						
Serum sample		**✓**				**✓**
Urine sample		**✓**				**✓**
Adverse event			**✓**	**✓**	**✓**	**✓**
Prescription		**✓**	**✓**	**✓**	**✓**	**✓**
Combined drugs		**✓**	**✓**	**✓**	**✓**	**✓**
Summary of the analysis						**✓**

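### The unadjusted between-arm t-test in section 3.1 is valid, but for visceral fat area and the continuous secondary outcomes it is generally less precise than a model that adjusts for the baseline value already collected

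*Protocol article*

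**What the plan says.** Section 3.1 makes the between-arm test depend on normality: if data are normal, an independent-sample t-test "will be used to assess the differences between the two groups, and a paired sample" t-test covers the before-after comparison. Otherwise a Wilcoxon signed-rank test is used. Neither branch uses a covariate, and no regression model is named for the clinical outcomes.

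The outcomes are defined as changes. Section 2.8.2 says of the primary outcome: "Changes in VFA will be compared between the two groups before and after treatment", and adds: "The indicator will be tested at baseline and week 12". Section 2.8.3 lists "Changes in metabolic parameters: glycated hemoglobin (HbA1c) levels, fasting plasma glucose (FPG") and the blood lipids among others, and states: "All measurements will be performed at baseline and at week 12". Table 1 agrees: the row "visceral fat area" is ticked at day 0 and at the 12-week visit.

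The sample size in section 2.10 rests on HbA1c ("treatment group: 6.94±0.88%, control group: 7.64±0.72%, mean difference between the two groups: 0.7" percentage points) and concludes: "a total of 76 patients will be required".

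**The concern.** Taken together, sections 2.8 and 3.1 describe a t-test on change from baseline. Subtracting the baseline fixes its slope at 1. ANCOVA estimates the slope from the data, and when the true slope is clearly below 1 it gives a smaller standard error for the same treatment difference. Every patient with a change value has a baseline value, so adjustment loses nobody and needs no new measurement.

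Precision matters most for VFA. It is a primary outcome, but the sample size was worked out for HbA1c and the protocol gives no expected difference or SD for VFA. With perhaps 38 evaluable patients per arm, a gain that costs no patients is worth having.

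**Working it through.** **Inputs from the protocol.** 76 evaluable patients, taken as 38 per arm (section 2.10, 1:1 allocation); α = 0.05, taken as two-sided; HbA1c SDs 0.88 and 0.72, difference 0.7.

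**Inputs assumed.** r from 0.5 to 0.9; k = week-12 SD / baseline SD, first 1 and then other values; a VFA difference of 0.5 SD for illustration.

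**The plan's own figure.** Root-mean-square SD = √((0.88² + 0.72²)/2) = 0.804. With difference 0.7 and 85% power this gives 48 patients in total (normal approximation) or 50 (t-test), not 76. The dropout step does work: 76/0.8 = 95, or 96 as 48 per arm. The mismatch is a separate matter; 38 per arm is used below only as the planned evaluable number.

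**Formulas.** Variance of the arm difference, in units of 2 × (baseline SD)²/n:
- t-test on change: 1 + k² − 2rk, which is 2(1 − r) when k = 1; 74 df.
- ANCOVA: k²(1 − r²) × 1.0139, where 1.0139 = 1 + 1/(76 − 1 − 3) is the cost of estimating the slope; 73 df.
- Before that cost, the change variance exceeds the ANCOVA variance by (1 + k² − 2rk) − k²(1 − r²) = (1 − rk)², which is never negative.

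**Equal SDs (k = 1).** Patient-equivalent gain = 2/(1 + r)/1.0139:

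| r | Gain | CI width, ANCOVA/change | Power at 0.5 SD, change → ANCOVA | Detectable difference at 85% power (SD), change → ANCOVA |
|---|---|---|---|---|
| 0.5 | 1.315 | 0.872 | 57.6% → 69.4% | 0.70 → 0.61 |
| 0.7 | 1.160 | 0.929 | 79.3% → 84.9% | 0.54 → 0.50 |
| 0.8 | 1.096 | 0.955 | 92.5% → 94.5% | 0.44 → 0.42 |
| 0.9 | 1.038 | 0.982 | 99.8% → 99.8% | 0.31 → 0.31 |

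Break-even: 2/(1 + r) = 1.0139, so r = 0.973.

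**Week-12 SD larger (k = 1.2).**
- r = 0.5: change 1.24, ANCOVA 1.08 × 1.0139; gain 1.13.
- r = 0.7: change 0.76, ANCOVA 0.7344 × 1.0139; gain 1.02.
- r = 0.8: change 0.52, ANCOVA 0.5184 × 1.0139; gain 0.99.

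At r = 0.8 the slope rk is 0.96, close to the 1 that the change score assumes, so only the cost of estimating it remains.

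**Week-12 SD smaller (k = 0.8).** r = 0.5: change 0.84, ANCOVA 0.48 × 1.0139; gain 1.73.

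**If the t-test were run on week-12 values.** The variance ratio is 1 − r², so the gain is 1/(1 − r²)/1.0139: 1.32 at r = 0.5, 1.93 at 0.7 and 5.2 at 0.9.

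**HbA1c.** 0.7/0.804 = 0.871 SD. With k = 1, power goes from 96.3% to 99.0% at r = 0.5 and from 99.8% to 99.9% at r = 0.7.

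**Validity.** In 40,000 simulated trials per r with no treatment effect, type I error was 0.049 to 0.050 for the change t-test and 0.047 to 0.050 for ANCOVA.

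**The case against.** The strongest reply is that nothing here is an error. A two-sample test on change is standard, unbiased and holds its type I error. That stands, and limits the point to precision. It does not remove it: the protocol names the unadjusted test, so this is a stated choice and not a detail left to a fuller document.

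Second, the size rests on figures that the protocol does not give. That also stands. A reader might take 4% to 32% as the range of the gain, or r = 0.97 as the point below which ANCOVA always wins. Both hold only with equal SDs; with k = 1.2 the gain is already gone at r = 0.8. The HbA1c SDs in section 2.10 differ between arms (0.88 and 0.72), so if the arms share a baseline SD, equality over time cannot hold in both.

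Third, the benefit for HbA1c is slight, and undocumented power for VFA is a sample-size matter. Both are correct. A reader might infer that the t-test leaves VFA underpowered, or that ANCOVA would settle its power. Without a VFA difference and SD, neither can be shown.

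Fourth, replacing only the t-test would leave the Wilcoxon rule standing for the same outcomes, and a log scale chosen after seeing skewness would be data-driven. Both are fair, and the fix must deal with them.

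**Conclusion.** The point holds as one of efficiency. For VFA, and for continuous secondary outcomes measured at baseline and week 12, the named test is generally less precise than baseline-adjusted ANCOVA. A reader might infer bias or an inflated type I error; the documents and the simulation support neither.

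The gain over a t-test on change is useful at low to moderate r with a stable or falling SD, and close to nil when r is high or the SD rises. On the less likely reading that the t-test is applied to week-12 values, the loss is larger. All figures rest on 38 evaluable per arm, two-sided 0.05, and assumed values of r and the SD ratio. The change is worth making for VFA; for HbA1c it serves consistency more than power. No claim is made about the TCM symptom score, whose scoring standard is in a supplement that is not shown.

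**What to change.** In section 3.1, for VFA first and likewise for HbA1c, fasting glucose and lipids:

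- Replace the between-arm t-test with ANCOVA of the week-12 value on arm and the baseline value of the same outcome. Report the adjusted mean difference with its 95% CI.
- Name in advance the outcomes to be analysed on the log scale at both times (for example triglycerides), reported as a ratio of geometric means with its 95% CI.
- State that this model replaces the normality check and the Wilcoxon rule for the between-arm comparison of these outcomes.

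No further covariate is needed. The cost is a few sentences and one model per outcome in SPSS, on data already collected. The model spends one degree of freedom (73 instead of 74), which adds about 1.4% to the variance. At worst, if r is high or the SD rises by week 12, precision falls by about 1%.

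### For non-normal outcomes, Section 3.1 names only the paired signed-rank test, so any such outcome in this two-arm trial has no valid between-arm test as written

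*Protocol article*

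**What the plan says.** Section 2.2 of the protocol article describes a "double-armed, parallel, randomized, controlled clinical trial" with 1:1 allocation, so the two groups are independent samples. Section 2.8.2 defines the endpoint: "The primary outcome is change in visceral fat area (VFA) and TCM syndromes efficacy score scale". It adds that "Changes in VFA will be compared between the two groups before and after treatment". Ultrasound steatosis grade is a secondary outcome in Section 2.8.3.

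Section 3.1 then assigns the tests:

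- **Normal data, between arms:** an independent-sample t-test, which "will be used to assess the differences between the two groups".
- **Normal data, before and after:** a paired t-test, whose stated purpose is "to compare the differences between groups before and after the intervention".
- **Non-normal data:** "Wilcoxon signed-rank test will be used for data that does not conform to normal distribution". No other test is named for these data.
- **Graded data:** "Grade data will be analyzed using Wilcoxon’s signed-rank test or the CMHχ2 test".

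The rank-sum (Mann-Whitney) test does not appear in the document.

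**The concern.** The question the trial asks is whether change differs between two independent arms. The signed-rank test answers a different one: whether the centre of a set of paired differences, or of a single sample, is zero. Applied as designed, it gives one before/after p-value per arm and no test of the treatment effect. For normal data the plan has both a between-arm test and a before/after test. For non-normal data only the before/after kind remains.

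This matters because both arms receive the same health education and lifestyle programme (Section 2.7), so both may improve without any effect of JTTF. A reader left with two within-arm p-values may be drawn to compare them, and a result that is significant in one arm and not in the other is weak evidence of a difference between arms. Either primary outcome could be affected if it fails normality.

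**Working it through.** No figure stated in the plan bears on the choice of test, so there is none to reproduce. The check has three parts.

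**1. Does each data type have a valid between-arm test in Section 3.1?**

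| Data type | Tests named | Valid between-arm test? |
|---|---|---|
| Continuous, normal | Independent-sample t; paired t | Yes, the independent-sample t |
| Continuous, non-normal | Signed-rank only | No |
| Graded | Signed-rank or CMH | Yes if CMH is chosen; no if signed-rank is chosen |

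The gap is the second row, together with the open choice in the third.

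**2. What happens if efficacy is read from within-arm tests?**

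Assume independent arms with the same true improvement, each within-arm test having power p. Then

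P(JTTF significant, control not) = p × (1 − p).

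- p = 0.30: 0.30 × 0.70 = 0.21
- p = 0.50: 0.50 × 0.50 = 0.25, the maximum of the formula
- p = 0.80: 0.80 × 0.20 = 0.16

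The values of p are assumed, since the documents give no within-arm power.

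A simulation agrees. Inputs: 38 per arm (half of the 76 evaluable patients in Section 2.10), normally distributed change scores, no treatment effect, both arms improving by an assumed 0.5 SD of the change score, 4,000 trials. Results:

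- signed-rank test significant within the JTTF arm: 84%
- significant in the JTTF arm only: 14% (the formula gives 0.841 × 0.159 = 0.134)
- rank-sum test on the change scores between arms: 5.0% rejections, the nominal level

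**3. What would baseline adjustment add?**

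With equal variances at baseline and week 12 and correlation r between them, in units of the outcome variance:

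- change score: 2(1 − r)
- ANCOVA: 1 − r²
- ratio: (1 − r²) / [2(1 − r)] = (1 + r)/2

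| Assumed r | Change score | ANCOVA | Ratio | Reduction |
|---|---|---|---|---|
| 0.5 | 1.00 | 0.75 | 0.75 | 25% |
| 0.7 | 0.60 | 0.51 | 0.85 | 15% |
| 0.8 | 0.40 | 0.36 | 0.90 | 10% |

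Both analyses are valid in a randomised trial. The difference is in precision.

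**The case against.** The best defence is that Section 3.1 is loosely worded but sound in intent. It does give a valid between-arm test for normal data, and CMH is a valid choice for steatosis grade. The paired t-test clause follows directly on the independent-sample t-test, so it most plausibly means change within each arm. Section 2.8.2 commits to comparing VFA changes between groups, and nowhere does the plan say that efficacy will be judged by contrasting within-arm p-values. An article also condenses a fuller document.

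Most of this stands, and it rules out several stronger readings that a reader might infer:

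- **That the between-arm comparison is invalid throughout.** It is not. The independent-sample t-test and CMH are both suitable.
- **That patients would be paired across arms.** Nothing in the document proposes this.
- **That the plan ignores baseline.** The primary outcome is a change score, so baseline enters. What is not stated is covariate adjustment, which an analysis plan may add.
- **That particular outcomes will be non-normal.** The article gives no distributions for them, so the number affected is unknown.

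What does not stand is the appeal to condensation. The article does not leave the non-normal test to another document. It names one, and that test cannot make the comparison.

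**Conclusion.** The point holds in a limited form. Section 3.1 misnames the test for non-normal continuous data and offers an unsuitable option for graded data. Any continuous outcome that fails normality, possibly a primary one, has no valid between-arm test as written. The paired t-test clause is a wording error.

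The size depends on how results would be read. The 21%, 25% and 16% figures are conditional: they apply only if efficacy is inferred by contrasting within-arm results, and they assume equal true improvement and the stated within-arm powers. They are not the plan's type I error, because the plan states no such rule. That a non-normal outcome has no between-arm test follows from the text alone and needs no assumption.

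The correction should be made. It concerns the test of the treatment effect, may reach a primary outcome, and costs almost nothing.

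**What to change.** Reword Section 3.1 as follows:

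- **Non-normal continuous outcomes:** compare changes between arms with the Wilcoxon rank-sum (Mann-Whitney) test.
- **Steatosis grade:** compare arms with the rank-sum test or the CMH row-mean-score test, and name which one.
- **Paired t and signed-rank tests:** restrict to descriptive before/after change within each arm, and correct the clause that says between groups.

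As an optional gain in precision, analyse week-12 VFA and TCM score by ANCOVA on arm and baseline value, and report the adjusted difference with its 95% confidence interval.

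The cost is a change of wording. It needs no new data, visits or patients, and the methods are standard. It should be settled before the interim analysis of the primary outcome at 50% enrolment (Section 3.2), so that the test is fixed before any outcome data are examined.
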